##### Nutritional assessments

Food intake will be assessed through the 24-h dietary recall (two working days and one weekend day). Twenty-four-hour dietary recall of the first day is completed at the same time as the first visit, and the record of the second and third days is completed by a trained questioner over the phone. Food notes will be taken from the participants every 2 weeks. The amount of consumption of all food and beverages is asked from the person based on household scales and recorded in the 24-h recall questionnaire. The 24-h recall questionnaires are reviewed by a nutrition expert after completion. Dietary data was analyzed by Nutritionist IV software (First Databank, San Bruno, CA, USA) modified for Iranian foods.

##### Biochemical assessment

Blood samples will be collected from the participants in the intervention on the first day and at the end of the intervention, observing 12–14 h of fasting. A 10-ml blood sample without any anticoagulant is centrifuged at a speed of 3500 rpm for 10 min. The serum separated from each person’s blood sample is transferred into sterile microtubes. The microtubes will be stored at − 80 °C.

##### Assessment of other variables

We will be used visual analogue scales [VAS] [47]; Depression, Anxiety and Stress Scale-21 Items (DASS-21) [48]; Pittsburgh Sleep Quality Index (PSQI) [49]; food cravings questionnaire [50]; the three-factor eating questionnaire-R21 [51]; and global acne grading system [52] to assess appetite sensations, mental health, sleep quality, food craving, eating behavior, and acne score of individuals, respectively. All these factors will be measured at onset and end of the study. The validity and reliability of the questionnaires have already been evaluated in Iran [53–58].

### Sample size calculation

By consideration of a type I error of 5% (*α* = 0.05), a power of 80%, according to the mean weight loss of 2.5 kg (a minimum clinically important difference) as the principal outcome and the standard deviation of 3.87 and 3.04 [59], the sample size was computed to be 25 for each group based on the two-sided t-test. Primary outcomes will be measured as a change from baseline. To compensate for an approximate drop-out rate of 5% during the study period, we elevate the final sample size to 30 subjects in each group. To calculate the required sample size Gigacalculator software was used.$$n=\frac{{\left({z}_{1-\frac{a}{2}}+{z}_{1-\beta }\right)}^{2}\left({{s}_{1}}^{2}+{{s}_{2}}^{2}\right)}{{\Delta }^{2}}$$

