### Study interventions

Participants will be randomly assigned (1:1:1) to one of the three groups for 8 weeks: (1) a 14:10 early TRF diet (eating ad libitum only between 8:00 AM and 6:00 PM) with probiotic supplementation; (2) an 14:10 early TRF diet (eating ad libitum only between 8:00 AM and 6:00 PM) with placebo supplementation; (3) a CR diet (energy-restricted 25% of required calories) with placebo supplementation as a control group.

During the TRF period, subjects are instructed to eat freely from 8:00 AM to 6:00 PM daily (for 10 h). While from 6:00 PM to 8:00 AM the next day (14 h), people will only be allowed to drink water, tea, and black coffee without sugar or any calorie-free drink. In addition, individuals will be suggested not to alter the composition of their usual diets throughout the TRF intervention. Furthermore, PCOS patients will be asked to consume a small handful of nuts consisting of 200 kilocalories of mixed nuts (18 g of fat, 5 g of protein, and 4 g of carbohydrates) during fasting if they experience drops in energy or severe headache [40].

In the CR diet of the control group, the daily calories will be calculated by a dietitian. Based on the Harris-Benedict formula, the basal metabolic rate (BMR) of patients will be calculated individually [41]. Then, the total daily energy needed by each person is calculated based on his physical activity and considering the thermogenic effect of food (TEF). Finally, 25% of the required calories [42] will be reduced. Subsequently, this daily caloric requirement will be divided into six-meal menus including 3 main meals and 3 snacks with a macronutrient ratio of 55% carbohydrates, 30% fat, and 15% protein. Based on this, a food menu will be prepared, and the necessary alternatives will be taught to the people of the control group. All participants will also take a probiotic or placebo supplement after breakfast with a glass of water.

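### The stated 25 per group for 80% power does not follow from the plan's own two-sided formula, which gives 31; the planned 30 per arm falls slightly short of 80% and holds no dropout margin

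*Protocol article*

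**What the plan says.** The Sample size calculation section of the protocol article sizes the trial on body weight, analysed as change from baseline. It sets a 5% type I error and 80% power and takes a "mean weight loss of 2.5 kg (a minimum clinically important difference) as the principal outcome", with "the standard deviation of 3.87 and 3.04" for the two groups. It prints the usual normal-approximation formula for two means, with the normal quantile at 1 − α/2 and the sum of the two variances. The result is reported as follows: "the sample size was computed to be 25 for each group based on the two-sided t-test". The next step reads: "To compensate for an approximate drop-out rate of 5% during the study period, we elevate the final sample size to 30 subjects" in each group. Under Study interventions the allocation is 1:1:1, so every pairwise comparison is between equal arms.

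**The concern.** All the inputs, the formula and the answer stand in one paragraph, and the answer does not come out of the formula. The gap is six patients per arm, too large to be rounding or a choice between normal and t quantiles.

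The paragraph tells a reader that the trial keeps 80% two-sided power down to 25 completers per arm, and that 30 contains a reserve for dropout. If the requirement is 31, neither statement is right. The error concerns the outcome that sized the trial, so a null result on weight would be judged against a power that the calculation does not support.

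**Working it through.** **Inputs, all from the Sample size calculation section:** two-sided α = 0.05 (z = 1.960); power 80% (z = 0.842); Δ = 2.5 kg; s₁ = 3.87; s₂ = 3.04; dropout 5%; 30 planned per arm.

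**Step 1: the plan's own formula.**
n = (z₁₋α/₂ + z₁₋β)² × (s₁² + s₂²) / Δ²

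- s₁² + s₂² = 14.977 + 9.242 = 24.219
- (1.95996 + 0.84162)² = 7.849
- n = 7.849 × 24.219 / 6.25 = 30.41, so **31 per group**, against the stated 25

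With the noncentral t distribution and Welch degrees of freedom, power is 79.4% at 31 and 80.7% at 32, so the t-test needs **32 per group**.

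**Step 2: what could produce 25?** Two departures from the stated inputs reach it.

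- *One-sided 5% test, both standard deviations as given.* The formula gives (1.64485 + 0.84162)² × 24.219 / 6.25 = 23.96, so 24. The one-sided t-test has 79.0% power at 24 and 80.4% at 25, so it needs 25.
- *Two-sided t-test with 3.04 used for both groups.* The smallest size reaching 80% is 25, with 81.3% power.

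The first contradicts the stated two-sided test, and the second contradicts the two stated standard deviations. Both also need the t distribution in place of the printed normal formula, which gives 24 in either case.

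**Step 3: power under the stated inputs** (two-sided, Δ = 2.5 kg, unadjusted):

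| Evaluable per arm | t-test (Welch) | Normal approximation | Difference detectable with 80% power (normal) |
|---|---|---|---|
| 25 | 70.1% | 71.9% | 2.76 kg |
| 28.5 (30 less 5%) | 75.9% | 77.4% | 2.58 kg |
| 30 | 78.0% | 79.5% | 2.52 kg |

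The last column is 2.8016 × √(24.219 / n). At the whole numbers on either side of 28.5, t-test power is 75.1% (28) and 76.6% (29).

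**Step 4: the dropout step.** Starting from 25, a 5% loss needs 25 / 0.95 = 26.3, so 27. Starting from the formula's 31, it needs 31 / 0.95 = 32.6, so 33; from the t-test's 32, it needs 32 / 0.95 = 33.7, so 34. That is 99 to 102 in total, against the planned 90. The 30 per arm is thus more than 5% loss would require if 25 were right, and one below the formula's requirement before any loss once 31 is used.

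**The case against.** **The practical shortfall is small.** This stands. The trial randomises 30 per arm, not 25. By the printed formula that is one patient per arm short before any loss, and after 5% loss the detectable difference moves only from 2.5 to 2.58 kg. A reader might infer that the trial has 70% power. That figure applies only if 25 per arm remain, a loss of 1 − 25/30 = 16.7%, which the plan does not expect.

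**The planned analysis is not a bare t-test.** The Statistical analysis section foresees a mixed linear model adjusted for confounders, which could recover some power. The amount depends on a correlation that the document does not give. As an assumption, if the covariates correlate r with weight change, the residual standard deviation shrinks by √(1 − r²). With r = 0.2, power is about 80% at 30 and 78% at 28.5; with r = 0.3, about 82% and 80%. The same section's correction for multiple comparisons works in the other direction. So the figures above are t-test power under the stated inputs, not the power of the final analysis. This does not repair the calculation, which is expressly for a t-test and takes no credit for covariates.

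**The software was set to a one-sided test.** A reader might infer this from how well 25 fits. The document names the software but not its settings, mentions no one-sided test, and gives inputs from which 25 can also be reached two-sided with the smaller standard deviation. The cause is unknown, and the error does not depend on it.

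**The step from 25 to 30 is a second error.** A reader might also infer this, since 5% would need only 27. But the dropout rate is called approximate, the text does not say that 30 equals 25 / 0.95, and 90 in total is a whole number of the blocks of six described under Randomization and blinding, whereas 81 (3 × 27) is not. Rounding up is harmless in itself. What fails is the base of 25, and with it the idea that 30 contains a reserve.

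**Conclusion.** The stated sample size is wrong as written. The plan's formula and inputs give 31 per group (32 by the Welch t-test), not 25. For a 2.5 kg difference, an unadjusted two-sided t-test has about 70% power at 25 per arm, 78% at 30 with no loss and 76% at 30 less 5%. The planned 30 therefore misses the stated 80% by about two to four percentage points and carries no dropout margin.

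These figures rest only on the plan's own difference, standard deviations, α and dropout rate. They make no allowance for covariate adjustment, the three-group comparisons or the second primary outcome. No other section of the article corrects the number, and an analysis plan that is not shown could not make the printed formula yield 25.

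**What to change.** Keep 30 per arm and correct the Sample size calculation section:

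- Delete the statement that 25 per group gives 80% power with a two-sided test.
- State instead that the formula gives 31 per group, and that 30 randomised per arm gives about 78% t-test power for 2.5 kg with no loss and about 76% with 5% loss, before any multiplicity correction or covariate adjustment.
- Replace the dropout sentence with a statement that 30 per arm includes no allowance for dropout. The step from 25 to 30 should not be re-described as a larger allowance, because 25 no longer serves as a base.

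The cost is wording only, with a slightly less favourable stated power and no extra patients. Restating the power is also the practical course, since the Trial status section expected recruitment to be almost finished on 23 September 2023, before the article was published.

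### The stated 5% drop-out does not explain raising 25 to 30 per group, and 30 with 5% loss gives about 76% power on the plan's own inputs, not 80%

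*Protocol article*

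**What the plan says.** Everything at issue stands in the section Sample size calculation of the protocol article. With a two-sided type I error of 5% and 80% power, the plan takes a "mean weight loss of 2.5 kg (a minimum clinically important difference) as the principal outcome" and "the standard deviation of 3.87 and 3.04", prints the usual normal-approximation formula for two means, and reports that "the sample size was computed to be 25 for each group based on the two-sided t-test". The next step is: "To compensate for an approximate drop-out rate of 5% during the study period, we elevate the final sample size to 30 subjects in each group".

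No other drop-out rate and no other reason for 30 appears in the article. The abstract repeats 30 per arm. The section Randomization and blinding fixes a block size of six with three arms, but the sample size section does not mention rounding to blocks. The section Statistical analysis keeps everyone who entered in the analysis and uses multiple imputation for missing data.

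**The concern.** A drop-out allowance links the number of women the analysis needs to the number enrolled. Here one figure is given on each side of that link and one rate between them, and the three do not fit together: the stated rate falls well short of the stated enrolment.

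At stake is what the power statement refers to. A reader would take the 80% as holding once the 5% loss has been absorbed. To check that, one needs the evaluable number the design expects and the power at that number. The article gives neither, and the explanation it offers for 30 cannot be used to recover them.

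**Working it through.** **Inputs, all from the section Sample size calculation:** difference 2.5 kg; SDs 3.87 and 3.04; two-sided 5%; power 80%; base number 25 per group; drop-out 5%; final number 30 per group. Block size six and 1:1:1 allocation come from Randomization and blinding and Study interventions.

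**Step 1. The plan's own step from 25 to 30.**
- Dividing by the retained fraction: 25/(1 − 0.05) = 26.3, so 27.
- Multiplying by one plus the rate: 25 × 1.05 = 26.25, so 27.
- Whole blocks: 27 × 3 = 81 is not a multiple of six. The next multiple is 84, or 28 per group. The planned total of 90 is 15 blocks, two per arm more than block rounding requires.

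The figure of 30 is not reproduced by either convention or by block rounding.

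**Step 2. What 30 would correspond to.**
- As a loss from those enrolled: 1 − 25/30 = 16.7%.
- As an add-on to 25: 30/25 − 1 = 20%.
- The word *approximate* does not bridge the gap: a 10% loss gives 25/0.90 = 27.8, so 28. Rounded up, 30 needs a loss above 1 − 25/29 = 13.8%.

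**Step 3. Evaluable number expected.** 30 × 0.95 = 28.5 per arm.

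**Step 4. The base number, needed to interpret power.** The printed formula gives

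n = (1.960 + 0.842)² × (3.87² + 3.04²) / 2.5² = 7.849 × 24.22 / 6.25 = 30.4, so 31 per group.

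The t-test that the text names needs 32. The 25 is not reproduced from the stated inputs. A one-sided test, or the smaller SD used in both arms, gives 24, which is close to 25, but each contradicts what the section states.

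**Step 5. Power on the stated inputs.** By normal approximation, power = Φ(2.5/√(24.22/n) − 1.960). At n = 28.5 this is Φ(2.712 − 1.960) = 77.4%. The last column uses the noncentral t distribution with Welch degrees of freedom.

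| Evaluable per arm | Situation | Normal | Welch t |
|---|---|---|---|
| 25 | plan's base number | 71.9% | 70.1% |
| 27 | 25 inflated for 5% loss, before any loss | 75.2% | 73.5% |
| 28.5 | 30 enrolled, 5% lost | 77.4% | 75.9% |
| 30 | 30 enrolled, none lost | 79.5% | 78.0% |
| 31 | printed formula | 80.7% | 79.4% |
| 32 | t-test requirement | 82.0% | 80.7% |

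The difference between 28.5 and 25 evaluable is 5.5 points (normal) or 5.8 points (Welch t).

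**The case against.** The strongest reply is that a surplus is not an error. Twenty-seven is a minimum, 30 more than covers a 5% loss from 25, and extra women raise power. That stands: enrolling more than 27 is not harmful, and nothing here argues for fewer.

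Several stronger readings are tempting, and the article does not support them.

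- *The plan carries two conflicting drop-out rates.* It does not. It states one, 5%. The 16.7% is a back-calculation, and 20% fits equally well under the other convention.
- *A reader cannot tell whether 28.5 or 25 evaluable women are expected.* The stated rate and enrolment together imply 28.5; 25 is the computed requirement. A loss of 10% to 15% would plainly exceed the stated assumption, whatever number was enrolled.
- *The drop-out sentence costs power.* It does not. If 25 really delivered 80%, then 28.5 would deliver about 85% (normal approximation), and both would meet the target. The figures below 80% come from the base number.
- *Thirty holds spare capacity for a loss of about 17%.* Only if 25 were enough. On the stated inputs, 30 falls just short of 80% even with no loss.

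Block rounding is a fair partial explanation. It narrows the gap from three women per arm to two, but the article does not invoke it and it stops at 28. The intention-to-treat analysis with multiple imputation does not settle the matter either: imputation keeps women in the analysis but does not in general restore the information in weights that were never measured.

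**Conclusion.** The step from 25 to 30 does not follow from its stated input. A 5% drop-out gives 27 per group, or 28 in whole blocks, and the article offers no other reason for 30. Taken alone this is a wording error in the safe direction.

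It matters because the sentence makes 30 look like a padded number. On the plan's own inputs, 30 enrolled with 5% lost gives about 76% power by the Welch t-test (77% normal), roughly three to four points below the stated 80%. The cause is the base number: 31 by the printed formula, 32 by the t-test. From those, a 5% loss would call for 31/0.95 = 32.6, so 33, or 32/0.95 = 33.7, so 34 per group.

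The power figures assume a comparison of two arms at an unadjusted two-sided 5%, the stated difference and SDs, and information equal to that from women with an observed outcome. Covariate adjustment or informative imputation could raise power somewhat; the article gives no figures from which to quantify that.

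**What to change.** Revise the sample size section as follows.

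- Keep 30 per group and the 5% rate.
- Delete the statement that the 5% drop-out accounts for raising 25 to 30.
- State that about 28.5 evaluable women per group are expected (30 × 0.95).
- Restate the power to detect 2.5 kg with SDs 3.87 and 3.04 at two-sided 5% as about 76%, falling to about 70% if only 25 per group remain.
- Do not describe 30 as containing reserve, and do not trim to 27. Trimming would give 73.5% (Welch t) before any loss.
- Correct the 25 at the same time, since the printed formula gives 31 and the restated power cannot be reconciled with 25 at 80%.

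The cost is a few corrected sentences and a less favourable stated power. Enrolment does not change, which suits a trial whose Trial status section expected recruitment to be nearly complete by 23 September 2023.

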### Data management and monitoring

In the baseline and post-intervention phases, data will be collected. CRFs (case report forms) will be used for recording participant data. Data entry and management will be done using an electronic database after CRFs are used for data collection. There will be two data collectors, and completed clinical raw data will be sent for approval to the project supervisor. Documentation is kept in a locked drawer, only accessible by the principal investigator. The forms contain an ID number unique to the participant and do not contain any information that can be used to identify the patient.

A clinical trial monitor occasionally supervises the study progress and ensures patient rights and well-being are safeguarded; the protocol, ethical requirements, standards, and regulations are being followed; the essential documentation is available; and collected data are accurate as there were recorded. One of the investigators will check the coding, security, and storage of data. In addition, she will evaluate data entry and data values twice. If any participant reports the occurrence of adverse events, more information is required to make a decision about excluding the participants from the trial. Unblinding is permissible in this situation based on the Medical Ethics Committee criteria. Ethical review of the data will be overseen by the Tehran University of Medical Sciences. Further, patients who discontinue the study or deviate from it will be provided with a list of all outcome data. Missing data will be imputed using modern methods for dropouts.

### Composition of the data monitoring committee

Participants are at minimal risk during the intervention and measurement protocols. Since this trial is low-risk, close monitoring by the principal investigator and an independent Safety Officer is part of the data safety monitoring plan. Any adverse event that exceeds the threshold and any serious adverse event will be promptly reported to the NIH and the COMIRB by the principal investigator and an independent Safety Officer. During the annual Safety Officer meeting, the Safety Officer will review the study coordinator’s reports to determine if any corrective action, trigger for an ad hoc review, or stopping rule violation should be reported to the study investigators, the COMIRB, and the sponsor.

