**Ethical aspects:**

The current trial received approval from the Medical Ethics Committee of Tehran University of Medical Sciences, Tehran, Iran (IR.TUMS.MEDICNE.REC.1401.425).

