### Randomization and blinding

A stratified permuted block randomization (a fixed block size of *n* = 6) was done using computer generated random numbers by the project coordinator. In this method, eligible patients who meet the study entry criteria are selected and then randomly allocated with stratification by BMI (between 25 and 30 and 30 and 35 kg/m^2^). People will be allocated to one of the three groups, IF diet with a probiotic supplement, IF diet with a placebo, and CR diet with a placebo. Random allocation will be based on a random number list; the letters A, B, and C will be assigned to an equal number of a random number list.

Placebo and probiotic supplements will be produced by TakGen Zist Pharmaceutical Company (Tehran, Iran) and will be placed in the same packages with similar color, flavor, and taste. Then packages will be placed in paper boxes and receive a special code. Placebo and probiotic supplement codes will remain with the company until the end of the study for blind researchers, laboratory staff, outcome assessors, and patients. However, no blinding will do in terms of diet (fasting or CR). In other hand, we do not anticipate any requirement for unblinding but if required, the trial manager, data coordinator, implementation support facilitators, and care home managers will have access to group allocations and any unblinding will be reported.

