### Statistical analysis

All analyses will be performed according to the Intention to Treat Analysis (ITT) method. Therefore, all participants who entered the study (regardless of whether they completed the 8-week study period) are included in the analysis. Missing data will be checked by multiple imputations. Statistical analysis will be conducted using the SPSS software (Version 24, SPSS Inc., and Chicago, IL, USA). The scatter diagram, histogram, and Kolmogorov–Smirnov test will be applied to examine the normality of the data. Normally distributed variables will be reported as the mean and standard deviation, while the median and interquartile range (IQR) will be used for reporting non-normally distributed variables. Moreover, we will use the chi-square test and Fisher’s exact test to compare categorical variables. Also, the independent sample *t*-test and Mann–Whitney U test will be applied to compare continuous variables between-group, whereas we will use paired sample *t*-test and Wilcoxon rank-sum test for within-group comparisons. To compare the differences in primary and secondary outcomes between the two study groups at the end of the trial and adjust the final findings for potential confounders, we will apply the mixed linear effect model. To correct for multiple comparisons and reduce alpha error, *q* values will be used using the Benjamin-Hochberg method. Based on this, significance was defined in *P* values less than 0.05 and *q* values less than 0.1. Cohen’s *d* will be calculated based on the mean and standard deviation. The effect sizes 0.20, 0.50, and 0.80, respectively for low, medium, and high therapeutic effects of the dietary intervention will be determined. No subgroup analyses are planned. However, no interim analyses are planned for this trial.

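### Serious adverse events are routed to two bodies with no other role in the document, while the Tehran ethics committee that approved the trial is never named as a recipient of safety reports

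*Protocol article*

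**What the plan says.** The reporting route stands in the Protocol article under Composition of the data monitoring committee. For adverse events beyond a threshold, and for serious ones, it states that "any serious adverse event will be promptly reported to the NIH and the COMIRB by the principal investigator and an independent Safety Officer". It then describes one scheduled review: "During the annual Safety Officer meeting, the Safety Officer will review the study coordinator’s reports". The officer decides there whether a corrective action, a trigger for an unscheduled review or a "stopping rule violation should be reported to the study investigators, the COMIRB, and the sponsor". The same section also promises close monitoring by the principal investigator and the Safety Officer.

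Elsewhere the ethics role belongs to Tehran. Under Ethical aspects: "The current trial received approval from the Medical Ethics Committee of Tehran University of Medical Sciences, Tehran, Iran". Under Study design, that committee, together with the Department of Clinical Nutrition, must confirm amendments and deviations. Under Data management and monitoring, the University oversees the ethical review of the data, and the committee's criteria decide whether unblinding is allowed after an adverse event.

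On the blind, Randomization and blinding says "Placebo and probiotic supplement codes will remain with the company until the end of the study". Later in the same paragraph it provides that, should unblinding be needed, three trial-level roles and "care home managers will have access to group allocations".

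**The concern.** The article does not leave the recipients open; it names them, and they do not match the body that it holds responsible for the trial everywhere else. Someone who followed the text literally would report a serious event to two organisations whose connection to a single-hospital trial in Tehran is not explained. Nothing in the text would tell that person to inform the committee that approved the study. That committee could then be asked to confirm a safety-related amendment, or to apply its unblinding criteria, without having received the report that prompted it.

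Two neighbouring statements fit the trial poorly in the same way: a yearly meeting for an 8-week intervention, and allocation access for a role that does not exist in this setting.

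**Working it through.** No formula applies to the main point, so the passages are set side by side. Simple date arithmetic is enough for the meeting.

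**1. Who does what**

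| Function | Body named | Section |
|---|---|---|
| Approval | Medical Ethics Committee, Tehran University of Medical Sciences | Ethical aspects |
| Confirming amendments and deviations | The same committee, with the Department of Clinical Nutrition | Study design |
| Ethical review of data | The University | Data management and monitoring |
| Criteria for unblinding after an adverse event | Medical Ethics Committee | Data management and monitoring |
| Receiving above-threshold and serious adverse events | NIH, COMIRB | Composition of the data monitoring committee |
| Receiving Safety Officer findings | Investigators, COMIRB, sponsor | Composition of the data monitoring committee |

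The first four rows and the last two share no oversight body. NIH appears once and COMIRB twice in the whole article, all in that one section, and neither is in the list of abbreviations. Study design gives a single site, Arash Hospital in Tehran.

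**2. When the annual meeting falls**

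Inputs: 8 weeks of treatment (56 days, and 56/365.25 = 15% of a year); Table 1 (recruitment in months 5–9, intervention in months 10–14, 18 months in all); Trial status (recruitment from 23 October 2022, almost finished by 23 September 2023, which is 335 days). The article does not say when the year starts, so the result is a range:

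- Table 1, year counted from month 1: the meeting comes at the end of month 12, within the intervention period of months 10–14.
- Table 1, year counted from the opening of recruitment: start of month 5 + 12 = start of month 17, after the intervention has ended in month 14. Everyone has finished.
- Table 1, year counted from the first intervention month: start of month 10 + 12 = start of month 22, beyond the 18-month timeline.
- Trial status dates, year counted from the opening of recruitment: the meeting is on 23 October 2023. Going back 56 days gives 28 August 2023, which is day 309. If treatment starts at enrolment, everyone enrolled by then has finished, and only those enrolled in the last 335 − 309 = 26 days are still treated. A participant enrolled on 23 September 2023 finishes on 18 November 2023.

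**3. Access to the codes**

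Randomization and blinding leaves the supplement codes with the manufacturer until the study ends, and lists roles that get the allocations if required. Data management and monitoring permits unblinding after an adverse event. Neither section says how a code held by the company reaches the listed roles, and one of those roles belongs to a setting that the trial does not use.

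**The case against.** The strongest reply is that naming two recipients does not exclude a third. The Tehran committee has a stated part in unblinding after adverse events and in safety-related amendments, so it may well be informed in practice. That is fair as far as it goes: the article does not say that the committee is barred from receiving reports. But the only explicit instruction on recipients leaves it out, and no other section puts it back.

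Several stronger readings are tempting and should not be drawn.

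- A reader might infer that safety is looked at only once a year. The documents do not support this: close monitoring, prompt reporting of serious events and triggers for unscheduled review are all stated, as are an occasional trial monitor and regular contact with participants. Only the scheduled meeting is annual, and its frequency does not decide who receives reports.
- A reader might attach one percentage to those who finish before the meeting. That needs a starting point for the year and an accrual pattern, neither of which is given, and Table 1 and Trial status lead to different answers.
- A reader might infer that no adverse-event threshold or stopping rule exists. The article condenses a full protocol that is not shown, and these may be defined there.
- A reader might set the statement that "no interim analyses are planned for this trial" against the safety review. A Safety Officer reading adverse-event reports is not an interim analysis of outcomes, so there is no conflict.
- A reader might call the code custody a flat contradiction. Custody by the company with an exception when required is a workable arrangement; what is missing is the link between the two, and one listed role is out of place.
- A reader might conclude that the text came from another trial's protocol. The article cannot show that, and the point does not need it.

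**Conclusion.** The point holds for the reporting route. As written, serious and above-threshold adverse events, and the Safety Officer's findings, go to bodies with no other role in the document, and the responsible Tehran committee is never named as a recipient. This rests on the text alone and needs no assumption beyond reading the named recipients as the intended ones. It changes no sample size, estimate or error rate; its weight lies in participant safety, and the low-risk description of the trial does not correct a misdirected report.

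The meeting interval is secondary. Across the starting points tried, the annual meeting falls anywhere from mid-intervention to after everyone has finished, so it fits poorly with 8 weeks of treatment without being the only safeguard. The misplaced role and the unexplained path to the codes are also secondary.

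**What to change.** - Reconcile Ethical aspects, Study design, Data management and monitoring, and Composition of the data monitoring committee by naming the Medical Ethics Committee of Tehran University of Medical Sciences as recipient of serious adverse event reports and of the Safety Officer's findings. If the NIH or the COMIRB does have a role, say what it is; otherwise remove them.
- Confirm, and record, that any serious events already observed reached the Tehran committee. Recruitment was due to be almost finished a month before publication on 25 October 2023, so correcting the text alone may come too late for most participants.
- State when the Safety Officer's year starts, and reconcile the timing of the meeting with Table 1 and Trial status. The timing itself is for the investigators and the committee to settle.
- In Randomization and blinding, remove the care home role and reconcile the paragraph with Data management and monitoring on who can obtain the codes held by the company, and how.

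The cost is wording in a few sections and one check of the safety records. The Safety Officer is already in place, so no post is added, and the analysis is unchanged.
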